**Table 4 T4:** 

Assessments at progressive disease (PD) during treatment
• Vital signs and ECOG • Laboratory tests: Hematology panel, chemistry panel • TSH, fT3/fT4 • C-lab blood sampling (20ml) for tumor-DNA • On site preparation and storage: blood sampling (50ml) for PBMC, arm B only (for both arms at site 01 Halle) • Adverse events • Concomitant medication • Radiological response (according to iRECIST) (routine diagnostics) until PD • If not done at screening: C-lab: Stored tumor tissue collection (paraffin block or 10 slides)

### Follow-up

2.5

All patients will be evaluated every 3 months after EOT until death or maximal 12 months after last patient in (**Table 5**). At progressive disease during follow-up (if not progressed during treatment), assessments will be done according to **Table 6**. All patients will be monitored 30 days after EOT for safety reasons (**Table 7**).

**Table 5 T5:** 

Follow-up
• Results of Radiological imaging (according to iRECIST) regarding disease status (from routine diagnostics) until PD • Pembrolizumab infusion is continued according to SmPC at the discretion of the physician • C-lab blood sampling (20ml) for tumor-DNA (only at FU1 and FU2) • Assessment of adverse events, concomitant therapies (only until FU1), subsequent anti-cancer therapies and survival status

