### Study objective

2.1

The primary objective of this study is to assess the efficacy of UV1 vaccination in combination with pembrolizumab in patients with R/M HNSCC and PD-L1 CPS ≥1 based on progression free survival according to iRECIST (progression-free survival rate at 6 months after randomization, PFS@6) (15).

Secondary clinical endpoints of this study are overall survival, objective response rate and duration of response according to iRECIST. Other secondary objectives are the UV1 vaccine induced immune responses and the clearance rate of ctDNA from blood during treatment. Additionally, this study will explore the safety and tolerability of UV1 vaccination in combination with pembrolizumab according to NCI CTCAE v5.0. Other objectives are the exploration of what patient subgroups benefit most from this combined approach and the establishment of liquid biopsy tumor monitoring in HNSCC.

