### Study design

2.2

The FOCUS trial is an open-label, randomized, phase II study which investigates the tolerability and efficacy of the UV1 vaccine in patients with R/M PD-L1 positive (CPS ≥1) HNSCC planned for first-line treatment with pembrolizumab. The study is multicentric and includes several study sites in Germany. 75 patients will be randomized with an estimated recruitment phase of 24 months. Planned duration of follow-up per patient is until death or 12 months after last patient in (**Figure 1**).

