**Table 3 T3:** 

Assessments during treatment
• Vital signs and ECOG (only for visit 1, 4, 5, 6, 7, 8 and EOT) • Laboratory tests: Hematology panel, chemistry panel (only for visits 1, 4, 5, 6, 7 and 8) • TSH, fT3/fT4 at visits 4, 5, 6, 7, 8 and EOT • Urine pregnancy test at visits 5, 6 and 7 • C-lab blood sampling (20ml) for tumor-DNA (only at visits 1, 5, 6, 8 and EOT) • On site preparation and storage: blood sampling (50ml) for PBMC, arm B only (for both arms at site 01 Halle) at visits 1 and 6 • Pembolizumab infusion (arm A) every 3 weeks according to the label at Visits 4, 5, 6, 7 and EOT (Visit 8) • Additional UV1 vaccination (arm B) 3 times the week before initiation of pembrolizumab followed by 5 additional applications on d1 cycle 1-5. • Adverse events • Concomitant medication • Radiological response (according to iRECIST) will be assessed at visit 8 (routine diagnostics)

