### Analysis of primary study endpoint

2.7

The primary study endpoint progression PFS@6 will be analyzed as the proportion of all intention-to-treat patients being known to be alive without progression at 6 months after randomization, providing the 95%, 90% and 80% confidence intervals for this estimate.

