### Statistics and data handling

2.8

The FOCUS trial is designed as a randomized phase II study to estimate the therapeutic effectiveness of pembrolizumab in combination with UV1 vaccination in relation to the standard treatment (single drug pembrolizumab). The assumptions on outcome after standard therapy is derived from available data and controlled for by a randomized reference (or calibration) arm. Due to this design, analysis of both treatment arms but no formal statistical comparison will be performed. All secondary endpoint analyses are considered explorative. Further clinical development of this combination depends on the primary endpoint (and its confidence interval), the findings in the control arm, and the supporting safety and feasibility findings.

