### Sample size estimation

2.9

The progression-free survival rate after 6 months (PFSR@6) with single agent pembrolizumab as first-line treatment in R/M HNSCC is about 25%. Pembrolizumab in combination with UV1 vaccination should result in a PFSR@6 of 40% to be regarded as promising for further development in a phase III setting. Based on these assumptions and by applying a one-sided test with an alpha error level of 0.1 and a beta error of 0.2 (corresponding to a power of 80%), 46 evaluable patients are needed in the experimental arm. According to the 2:1 randomization, about 23 patients will be included in the control arm. To allow for a 10% drop out rate, a total of 75 patients should be included.

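### The trial is open-label and PFS@6 is taken from routine scans with no masked reading described; a few favourable misreads confined to Arm B would exceed the planned 10% error level, and masking the existing read is cheap

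*Protocol article*

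**What the plan says.** Section 2.2 states: "The FOCUS trial is an open-label, randomized, phase II study". Section 2.1 sets the primary objective on "progression free survival according to iRECIST (progression-free survival rate at 6 months after randomization, PFS@6"), and section 2.7 analyses it as the "proportion of all intention-to-treat patients being known to be alive without progression at 6 months after randomization".

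The disease status behind that proportion is scheduled in four tables, and each names routine diagnostics as the source. Table 3 says "Radiological response (according to iRECIST) will be assessed at visit 8 (routine diagnostics"), and Table 5 says "Results of Radiological imaging (according to iRECIST) regarding disease status (from routine diagnostics) until PD". Tables 4 and 6 do the same for the visit at progression, during treatment and during follow-up. No table or section says who applies iRECIST, or whether that person knows the arm.

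Section 2.9 plans on a PFS rate that "with single agent pembrolizumab as first-line treatment in R/M HNSCC is about 25" per cent, and says the combination "should result in a PFSR@6 of 40% to be regarded as promising for further development in a phase III setting". Section 2.8 rules out a formal statistical comparison of the arms and adds: "Further clinical development of this combination depends on the primary endpoint (and its confidence interval), the findings in the control arm", together with safety and feasibility. It gives no numerical go rule.

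**The concern.** PFS@6 mixes deaths, which cannot be re-read, with radiological progressions, which involve judgement. When the reader knows which patients were vaccinated, a borderline scan may be called differently in the two arms. Objective response rate and duration of response rest on the same calls.

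The design gives little protection against this. Arm B is tested against a fixed 25%, so a bias common to both arms would show up as a control rate above that figure, but a bias confined to Arm B would not. About 25 controls and no formal comparison make a weak check in any case. At stake is whether a result that supports a phase III trial reflects the vaccine or the reading.

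**Working it through.** **Inputs.** Null rate 25%, target 40%, one-sided alpha 0.10, power 80%, 46 evaluable patients in the experimental arm (all section 2.9); about 50 patients in Arm B (section 2.3); 80%, 90% and 95% confidence intervals (section 2.7).

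**Step 1: reproduce the plan's figure.** Find the smallest n for which some cut r satisfies P(X ≥ r | n, 0.25) ≤ 0.10 and P(X ≥ r | n, 0.40) ≥ 0.80, with X binomial. The answer is n = 46 with r = 16 (34.8%): type I error 0.0896, power 0.8078. The stated 46 is therefore an exact single-arm test. A two-arm comparison at 2:1 would need about 66 controls, not about 23.

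**Step 2: the cut for about 50 intention-to-treat patients.** The smallest r with P(X ≥ r | 50, 0.25) ≤ 0.10 is 17 (34%): type I error 0.0983, power 0.8439. The same cuts follow from the 80% interval that section 2.7 plans, if it is computed exactly (Clopper-Pearson). Its lower limit first passes 25% at 16/46 (25.4%; 15/46 gives 23.4%) and at 17/50 (25.1%; 16/50 gives 23.2%).

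**Step 3: add k favourable misreads.** Suppose the true rate is 25% and k true failures in Arm B are recorded as progression-free. The observed count is X + k, so the false-positive rate is P(X ≥ r − k | n, 0.25).

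| Cut | k = 0 | k = 1 | k = 2 | k = 3 |
|---|---|---|---|---|
| 16/46 | 0.0896 | 0.1535 | 0.2432 | 0.3575 |
| 17/50 | 0.0983 | 0.1631 | 0.2519 | 0.3630 |
| 19/46 (observed ≥ 40%) | 0.0111 | 0.0242 | 0.0484 | 0.0896 |
| 20/50 (observed ≥ 40%) | 0.0139 | 0.0287 | 0.0551 | 0.0983 |

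**Step 4: how often would the calls change the verdict?** At 17/50 under the null, one call matters only if the true count is 16: 0.1631 − 0.0983 = 0.065. Three calls matter only if it is 14 to 16: 0.3630 − 0.0983 = 0.265. In most null trials the verdict would not change.

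**Step 5: misreading as a rate.** Assume that a share s of failures is radiological and a fraction m of those is misread. The apparent rate is then 0.25 + 0.75·s·m. The documents give neither s nor m, so a range is shown. At 17/50 with m = 5%, the false-positive rate is 0.16 (s = 50%), 0.19 (s = two thirds) or 0.21 (s = 80%). With m = 10% it is 0.25, 0.32 or 0.37.

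**The case against.** **The article is condensed.** A reader might infer that the scans are read locally by someone who knows the arm. The documents do not support that as a fact. Open-label describes the treatment, and routine diagnostics describes where the scans come from; neither identifies the reader or what the imaging request contains. A masked or central read is not mentioned, but it is not excluded either, and the full protocol may provide one. This stands: the point is that no masking is described, not that none exists.

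**The cut of 17/50 is not stated.** Section 2.9 attaches the word promising to 40%, and requiring an observed 40% keeps the error below 10% with up to three misreads. It is right that no numerical go rule exists and that the inflation depends on which bar is used. But 40% cannot be the cut of the planned test. At a true 40%, the power would be 0.48 for 19/46 and 0.55 for 20/50, against the stated 80%. The cut that fits the stated alpha and power is 16/46. It is also true that at 17/50 the lower limits of the 90% and 95% intervals (23.0% and 21.2%) do not pass 25%.

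**The bias is hypothetical.** A reader might take the table as a forecast. It is not one: every scenario puts all errors in one direction and in Arm B only, and the documents give no misreading rate. Both arms receive pembrolizumab, so borderline scans will arise in both. Counting unknown status as failure also works against a false positive. All of this stands, and it makes the figures a measure of sensitivity only.

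**Conclusion.** The concern holds in limited form. The article fixes an open-label design, takes the iRECIST calls behind PFS@6 from routine diagnostics, tests Arm B against a fixed rate and makes no formal between-arm comparison. It describes nothing that would keep the arm from the reader. Under the test implied by the sample size, a single favourable misread confined to Arm B is enough to exceed the planned 10% error level, and three bring the false-positive rate to about 36%.

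This rests on three assumptions: the implied cut is the one that guides the decision, the misreads favour Arm B only, and the full protocol does not already mask the reading. The stronger claim, that a few calls will produce a false promising result, is not supported. This is an inexpensive improvement to a defensible design, not an error in the plan.

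**What to change.** Keep the open-label design and the existing reading. State in sections 2.4 and 2.5 and in Tables 3 to 6 that, for every on-study scan up to PD in both arms, arm and vaccination status are left off the imaging request. The site radiologist who already reads the scan records the iRECIST category before the arm is disclosed. The clinical report may then use full treatment information. The instruction has to cover every scan, because nobody knows when requesting a scan whether it will decide the 6-month status. If the full protocol already provides this or another masked read, one sentence saying so settles the point.

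The cost is a short protocol text and a site instruction, with no extra reader, scan or patient. There are two small downsides. The reader may learn the arm from the hospital record, and may lack vaccination information when first judging nodes that drain the injection site.

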**Table 6 T6:** 

Visit at PD during follow up (if not progressed during treatment)
• Results of Radiological imaging (according to iRECIST) regarding disease status (from routine diagnostics) • Subsequent anti-cancer therapies • C-lab blood sampling (20ml) for tumor-DNA • Survival and disease status • Assessment of adverse events, concomitant therapies and subsequent anti-cancer therapies • Blood sampling (50ml) for PBMC (on site preparation and storage) arm B only (for both arms at site 01 Halle) • If not done at screening: C-lab: Stored tumor tissue collection (paraffin block or 10 slides)

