**Table 2 T2:** 

Baseline assessment
• Informed consent • Review of inclusion and exclusion criteria • Relevant medical history • Laboratory tests: Hematology panel, chemistry panel, including also TSH, fT3/fT4, PT/PTT, INR/Quick • Hepatitis B/C screening test, HIV screening test (not older than 4 weeks before randomization) • Physical examination • Vital signs and ECOG • Radiological imaging by computertomography of the neck, chest, abdomen and pelvis (according to RECIST v1.1, not older than 4 weeks before randomization) • Urine pregnancy test • Concomitant medication • C-lab: Stored tumor tissue collection (paraffin block or 10 slides), remaining tumor tissue from the first diagnosis or at relapse • C-lab: Fecal sample

Assessments during treatment will be done on visit 1 (week 1 [W1] day 1 [D1]), visit 2 [W1 D3], visit 3 [W1 D5], visit 4 [W2], visit 5 [W5], visit 6 [W8], visit 7 [W11], visit 8 [W14] and end of treatment (EOT) according to **Table 3**. Screening and visit 1 can be performed on the same day. Assessments at progressive disease (PD) during treatment (if applicable) will be performed according to **Table 4**.

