**Table 8 T8:** 

Translational work-up
• Immunohistochemistry (IHC) for PD-L1 to deduce tumor proportion score (TPS), immune cell (IC) score and combined positivity score (CPS), and IHC for telomerase tissue expression • Next-generation T cell receptor repertoire sequencing of circulating and tumor-infiltrating lymphocytes (TiL) • Next-generation gene panel sequencing for mutational profiling of tumor or circulating tumor DNA (ctDNA, liquid biopsy) • In individual patients liquid biopsy courses will be confirmed with digital droplet PCR (ddPCR) as an alternative methodology • Immune response assays against hTERT peptides measured by 3H-Thymidine proliferation and IFNgamma ELISPOT assays

In centers with expertise in collecting and locally freezing peripheral blood mononuclear cells (PBMCs), additional blood will be collected at visit 1, 6 and at PD from patients receiving UV1 vaccination (from patients of both arms only at site 01 Halle only) for immune response assays (**Table 8**).

Tumor tissue acquired before treatment initiation at first diagnosis or at relapse (biopsy of primary tumor, surgical material, or biopsy material of metastatic lesions) and potential biopsy or surgical material acquired during the study will be analyzed (**Table 8**, **Figure 2**).

Fecal samples will be collected prior to treatment to evaluate the gut microbiome (**Table 8**).

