To identify potential patients that benefit most from the combination of UV1 and pembrolizumab and to uncover potential mechanisms of resistance, the FOCUS trial is accompanied by a biomarker program which includes assessment of tumor biopsies prior to treatment, immunomonitoring by next-generation sequencing (NGS), and liquid biopsy monitoring of tumor subclones during treatment.

The peripheral blood T cell space shows age-specific architectures with cancer patients overall displaying reduced repertoire richness and diversity (29). Previous studies showed that immune checkpoint blockade led to diversification of the peripheral blood T cell space in patients with melanoma and other solid tumors, which was associated with response to treatment in some studies (30–32). In the FOCUS study, the characteristics of tumor-infiltrating lymphocytes and blood-circulating T cells will be studied by NGS and immunological analyses will be correlated with vaccine-specific immune responses assessed by standardized T cell proliferation assays.

Furthermore, tumor tissue and liquid biopsy testing will be done at baseline using a gene panel which covers frequent driver and resistance mutations in HNSCC. The circulating tumor DNA clearance over time will be correlated with overall response, progression-free survival, and overall survival. To search for tumor subclones potentially resistant to pembrolizumab or UV1, the liquid biopsy panel includes genes involved in resistance to checkpoint inhibitors as well as the coding region of hTERT as the UV1 target.

In conclusion, the FOCUS trial investigates the potential synergistic effect of UV1 vaccination and checkpoint blockade with pembrolizumab in patients with R/M HNSCC. To optimize tumor response in this often frail and pretreated patient population, an extensive biomarker program accompanies the FOCUS trial.

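### Stored tumour tissue missed at screening is requested again only at progression, so among those patients the availability of tissue markers depends on outcome

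*Protocol article*

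**What the plan says.** Table 2 of the protocol article makes tissue a baseline item for every patient: "C-lab: Stored tumor tissue collection (paraffin block or 10 slides), remaining tumor tissue from the first diagnosis or at relapse". The two tables for visits at progression, Table 4 (during treatment) and Table 6 (during follow-up), then each carry a conditional line: "If not done at screening: C-lab: Stored tumor tissue collection (paraffin block or 10 slides".

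The tables that apply without progression have no tissue line. These are Table 3 (treatment visits), Table 5 (follow-up) and Table 7 (safety follow-up). Blood is handled differently: Table 5, for example, schedules "C-lab blood sampling (20ml) for tumor-DNA (only at FU1 and FU2" with no progression condition.

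Section 2.6 states which tissue will be analysed, beginning with "Tumor tissue acquired before treatment initiation at first diagnosis or at relapse", and adds material that happens to be taken during the study. It sets no further time at which missing stored tissue is requested.

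On purpose, section 2.1 says "Other objectives are the exploration of what patient subgroups benefit most from this combined approach", and the Discussion introduces the biomarker programme with the words "To identify potential patients that benefit most from the combination of UV1 and pembrolizumab".

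**The concern.** A baseline marker should be available, or missing, for reasons unrelated to what happens to the patient later. Here a patient whose block was not sent at screening gets a second request if the disease progresses and, by the tables, none otherwise. In that subset, having a marker value is partly a consequence of the outcome that the marker is meant to explain. The patients left out for good are those with the most lasting benefit.

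The assays exposed are those in Table 8 that need tissue: PD-L1 scoring on the submitted block, telomerase immunohistochemistry, T cell receptor sequencing of tumour-infiltrating lymphocytes, and the gene panel when run on tumour. At stake are the progression-free rates within marker groups, and the differences between them, in an exploratory objective of the trial.

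**Working it through.** **1. The schedule side by side**

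| Table | Applies to | Request for stored tissue |
|---|---|---|
| 2 | all patients, baseline | yes |
| 3 | treatment visits | none |
| 4 | progression during treatment | if not done at screening |
| 5 | follow-up | none |
| 6 | progression during follow-up | if not done at screening |
| 7 | safety follow-up | none |

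**2. Inputs**

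- q, the true progression-free share at 6 months. Section 2.9 says the combination "should result in a PFSR@6 of 40% to be regarded as promising", so q = 0.40 for arm B. It says the rate "with single agent pembrolizumab as first-line treatment in R/M HNSCC is about 25" percent, so q = 0.25 for arm A.
- Arm B has about 50 patients (section 2.3).
- m, the share without tissue at screening. The article does not give it. Assumed 10% to 30%, unrelated to later outcome.

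**3. Lowest rate for a given m**

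Suppose every progressor without tissue is caught up, and no patient who is progression-free at 6 months ever is. Then

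rate in tissue set = q(1 − m) / [q(1 − m) + (1 − q)]

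| m | q = 0.40 | q = 0.25 |
|---|---|---|
| 10% | 0.36/0.96 = 37.5% | 0.225/0.975 = 23.1% |
| 20% | 0.32/0.92 = 34.8% | 0.20/0.95 = 21.1% |
| 30% | 0.28/0.88 = 31.8% | 0.175/0.925 = 18.9% |

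For 50 patients in arm B, 20 of them progression-free, m = 30% removes 6 of the 20 and gives 14/44.

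**4. Later progressors bring the rate back up**

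Follow-up runs until death or 12 months after the last patient in (sections 2.2 and 2.5), and Table 6 catches up anyone who progresses in that time. Only patients still progression-free at study end stay without tissue. The article gives no figure for them, so these are assumed illustrations in 50 patients with 20 progression-free at 6 months:

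- 5 still progression-free at study end, m = 20%: 1 lost, (20 − 1)/(50 − 1) = 19/49 = 38.8%.
- 7.5 still progression-free, m = 30%: 2.25 lost, 17.75/47.75 = 37.2%.

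**5. Deaths without a progression visit push the same way**

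These are events that also miss the catch-up. In the limit where no event is caught up, the rate is q(1 − m)/[q(1 − m) + (1 − q)(1 − m)] = q. The figures in step 3 are therefore floors for the given m.

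**6. Comparison between marker groups**

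Assume true rates of 55% and 25% in two marker groups, and m = 20% in both, under the step 3 conditions.

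- Rates: 0.44/(0.44 + 0.45) = 49.4% and 0.20/(0.20 + 0.75) = 21.1%.
- Difference: 28.4 points instead of 30.
- Odds ratio: before, (0.55/0.45)/(0.25/0.75) = 3.67; after, (0.44/0.45)/(0.20/0.75) = 3.67, unchanged.

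The odds ratio is preserved because missingness here depends on outcome alone. If m differed between the groups (m₁ and m₂), the observed odds ratio would be the true one times (1 − m₁)/(1 − m₂). The article gives nothing from which to judge whether it does.

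**7. Primary endpoint and sample size**

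Section 2.9's 46 evaluable patients reproduce with an exact one-sample binomial test. Requiring at least 16 of 46 gives a one-sided error of 0.0896 at 25% and power of 0.808 at 40%. Tissue does not enter this calculation, nor the intention-to-treat analysis in section 2.7.

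**The case against.** The strongest reply is that the point is partly an inference from absence. Figure 2, the study schedule, is not shown, and the full protocol is not at hand. Section 2.6 attaches no progression condition to the analysis of pre-treatment tissue, and nothing bars a site from sending a block late. This stands as a limit: another collection point may exist. It does not remove the point, because the tables are itemised by visit and the catch-up line is written out twice, each time under progression.

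A reader might infer that progression-free patients in general drop out of the biomarker set. The documents do not support that. Only patients without screening tissue are affected, and only for tissue-based assays. Blood for tumour DNA and immune analysis is scheduled without requiring progression, and the fecal sample is taken before treatment. The gene panel can also be run on circulating tumour DNA, with liquid biopsy planned at baseline. CPS of at least 1 is an eligibility criterion, so CPS is known before randomisation.

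A reader might also take 31.8% as the expected rate. It is a floor under an assumed m, and steps 4 and 5 both move it towards 40%. Nor does any section plan to set marker subgroups against the 25% and 40% figures, which belong to the sample size. Section 2.8 calls all secondary analyses explorative.

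**Conclusion.** The point holds in a limited form. Under the visit tables shown, among patients without screening tissue, availability of tissue-based baseline markers depends on progression, and those still progression-free at the end of follow-up are not caught up.

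The size is unknown because the share without screening tissue is not stated, and it may be small. For an assumed 10% to 30% and a true rate of 40%, the tissue-set rate at 6 months lies between a floor of 37.5% to 31.8% and the true 40%. This rests on screening availability being unrelated to outcome. Rates within marker groups and their differences are distorted; the odds ratio is not, if missingness depends on outcome alone.

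The case for changing the schedule is that the dependence is avoidable at little cost, not that it threatens the trial's main result.

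**What to change.** Add to Table 3 a request for missing stored pre-treatment tissue from every patient, regardless of disease status, at a fixed early treatment visit, and repeat it at visit 8/EOT. Keep the lines in Tables 4 and 6 only as a backstop. Replacing them with a request at visit 8/EOT alone would miss patients who progress or die before that visit and create selection in the other direction; the early request is there to prevent this.

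Report tissue availability by arm and by outcome. Run the tissue-based subgroup analyses with and without samples obtained only because of progression.

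The tissue is already stored, so no biopsy and no extra visit are needed. The cost is some additional archive retrieval for patients who have not progressed.
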